**Enhancing Dementia Instruction and Tool in Home Hospice Care (EDITH-HC)**

**Research Protocol**

##### 1. Purpose.

This research study is intended to improve the quality of care provided to home hospice PLwD and their FCP. The purpose of this study is to develop and preliminary test an educational training program and family care partner (FCP) assessment tool for hospice nurses and social workers (clinicians)to improve clinician knowledge about end-of-life care for persons living with dementia (PLwD) and to improve support for and reduce burden among FCP of home hospice PLwD.

##### 2. Specific Aims.

The Specific Aims of the study are:

**Aim 1.** To refine dementia-focused training materials and create a goal assessment tool for home hospice clinicians to guide care and support for PLwD and FCP. Sub Aim 1. Incorporate perspectives of Black and white stakeholders (iterative feedback with engagement with 10 FCP, 5 clinicians, 5 research/content experts).

**Aim 2.** To examine feasibility and acceptability of the training and tool and revise them based on feedback. (single-armed pilot study with 1-2 hospice clinical teams (10 clinicians) and FCP (10).

**Aim 3.** To conduct a randomized pilot test to determine the feasibility and acceptability of implementing the training and tool in clinical practice and the preliminary efficacy of the training and tool compared to usual care. (two-armed randomized study with up to 14 hospice clinical teams and FCP of PLwD assigned to the clinical teams: approximately 12 clinicians and 48 FCP will be randomized to receive the intervention and approximately 12 clinicians and 48 FCP to the usual care arm. We may enroll up to 18 clinicians in each arm to allow for attrition and some clinicians not matching with 4 caregivers to reach goal of 48 FCP in each arm. Clinicians and FCP will be randomized to intervention or usual care groups by clinical team using an adaptive randomization approach that strives to maintain balance between number of Black and White caregivers in each study arm.

##### 3. Study design

This study proposes to develop and pilot test a two-part intervention, Enhancing Dementia Instruction and Tool in Home Hospice Care (EDITH-HC), that provides 1) educational videos for hospice nurses and social workers (clinicians) about dementia-specific end-of-life care and 2) an assessment tool for clinicians to use as part of their clinical practice to use with FCP to identify and address dementia-related stressors for FCP of home hospice PLwD. This study will use a mixed-methods design including intervention refinement and pilot testing. To achieve **Aim 1** we will obtain 2 rounds of structured, key stakeholder input from 10 FCP, 5 hospice clinicians, and 5 research/content experts. We will use this input to refine training materials and a tool for clinicians. The training and tool will help home hospice clinicians identify and suggest tailored strategies to address common and distressing challenges for PLwD and FCP. For **Aim 2**, we will test the training and tool with 1-2 clinical teams of 8-12 hospice clinicians and 10 Black and white FCP to determine feasibility and acceptability. We will revise the training and tool based on feedback. For **Aim 3** we will conduct a randomized pilot study to determine the feasibility and acceptability of implementing the training and tool in clinical practice compared to usual care. We will also determine preliminary efficacy of the training and tool. Outcomes include: feasibility and acceptability of the intervention, improving clinician knowledge and confidence (*secondary outcomes*), reducing FCP burden (*primary outcome*), and increasing FCP preparedness and self-efficacy, and decreasing PLwD hospice disenrollment *(secondary outcomes)*.

## **Aim 1: EDITH-HC Training and Tool Development**

**Educational Videos.** We will develop and refine 5, 5-10 minute videos, addressing topics or challenges FCPs frequently encounter in dementia caregiving at EOL, including, but not limited to, knowing what to expect as dementia progresses (Video 1), feeding as EOL approaches (Video 2), and symptom management (Video 3); and instructions on how to use the assessment tool (Video 4) and complete the care partner burden assessment embedded in the hospice’s electronic health record (EHR) (Video 5). Video content will draw upon literature review and information from prior interviews with clinicians and FCP. We will receive feedback on the videos from Black and white FCP, clinicians, and research/content experts using a modified Delphi approach incorporating user-centered design protocol (below). Videos will contain relevant information, strategies for addressing FCP challenges, and a case study to which clinicians can apply information and strategies. Providing the training in a video format will allow clinicians to complete the training at their convenience or as in-service modules, reducing burden. We will take steps to have the training count as continuing education units. Additional video topics may be developed depending on the needs of the clinicians and FCP.

**Assessment Tool.** We will develop and refine an assessment checklist adapted from a previously validated dementia caregiving burden assessment tool that focuses on and incorporates care partner burden and challenges specific to the home hospice setting. To limit burden on clinicians and FCP, the tool will provide clinicians with a series of prompts and strategies to address FCP problems identified using the assessment tool. The tool will support clinicians and FCP to identify multiple strategies for addressing issues, decide which strategy will be most effective, and devise a plan to implement the most effective strategy. The tool will be designed so that it can complement and be incorporated into standard hospice care planning. Clinicians will be trained to use the assessment tool in an educational video (previous section). We will receive feedback on the tool from Black and white FCP, clinicians, and research/content experts using a user-centered design protocol (below).

**Modified Delphi Approach with User-centered Design.** After the initial prototype development of the intervention, we will use a modified Delphi approach incorporating user-centered design process to refine the intervention. We will gather two rounds of structured feedback from key stakeholders including clinicians (5), Black (5) and white (5) FCP, and content/research experts (5). Participants will be asked to comment on the clarity and relevance of training and tool content and the feasibility of suggested strategies using structured and semi-structured interview questions. We will review and compile responses, revise intervention materials based on feedback, and request additional feedback from key informants. Informant feedback will be provided in 30-60 minute follow-up telephone, video-conferenced, or in person interviews within 4 weeks of receiving intervention materials. Clinicians and FCP will be interviewed individually and recruited from VNS Health, formerly Visiting Nurse Service of New York (VNSNY), and will be compensated $50 for each round of feedback. Research/content experts will be identified based on their expertise and compensated $250. Data collected during this process is outlined in the Appendix. Further information related to recruitment, participant inclusion/exclusion criteria, and informed consent forms are detailed in other sections of the protocol.

## **Aim 2: EDITH-HC single armed pilot study**

The aim of the single armed pilot study will be to examine feasibility and acceptability of the intervention and finalize intervention materials. Clinicians from a 1-2 VNS Health interdisciplinary teams (IDT) will be asked to view the videos and review the tool, either as part of a team meeting or on their own time. They will be asked to provide feedback after viewing each video and the tool online or via telephone or videoconference. Study staff will follow up with clinicians by phone or teleconference to collect incomplete data. FCP will review the tool with a VNS Health clinician from the IDT testing the intervention and be asked to provide feedback on it via telephone or videoconference with a member of the research team. We will obtain participants’ perceptions on feasibility of the videos and tool including utility of the individual modules, training appropriateness, and fit within organizational culture. We will evaluate the tool using a “think aloud” strategy with FCP and hospice clinicians. We will finalize the training and tool based on results from the interactive sessions. We will recruit 10 clinicians from 1-2 clinical hospice teams to test the training and tool and 10 FCP (5 Black, 5 white) to test the tool. Data collected during this process is outlined in the Appendix. Based on data, we will modify the data collection protocols and intervention before conducting the pilot RCT (Aim 3).

**Hypotheses**. >70% of participants will: 1) complete the training, 2) report the training and tool are useful, 3) increase knowledge of dementia-related challenges and care strategies, and 4) increase confidence in providing dementia-related care.

**Measurements.** All participants will be assessed on the measures listed in Table 1 (see **Appendix** for more details). Measures will be administered at baseline immediately following intervention receipt. Participants will be compensated $50 for providing feedback on the training and $50 for providing feedback on the tool. Data collected in Aim 2 will allow identification of study design issues that may not arise in Aim 1 and will provide opportunity to make refinements to the intervention before proceeding with the full pilot RCT study (Aim 3).

## **Aim 3: EDITH-HC pilot RCT**

Based on a contracted healthcare work force following the COVID-19 pandemic and resulting smaller clinical teams, we are requesting to reduce the estimated enrollment of clinicians and FCP for the pilot RCT. While we will continue to enroll as many eligible participants as possible, the range of expected participants in the following sentences represent expected “worst” and “best” case scenarios for enrollment. For Aim 3, approximately 24 clinicians and 96 Black and White FCP will be recruited from up to 14 hospice clinical teams, although we may enroll up to 18 clinicians in each arm, for up to 36 clinicians in total. The intervention will be randomized by hospice clinical team using an adaptive randomization approach that strives to maintain balance between number of Black and White caregivers in each study arm. Approximately 12 clinicians and 48 FCP will receive the intervention and 12 clinicians and 48 FCP will receive standard home hospice care, but we may enroll up to 18 in each arm to allow for clinician attrition and some clinicians not matching with 4 caregivers to reach goal of 48 FCP in each arm. The intervention will last for a few to several months, depending on the timing of FCP enrollment and routine hospice visits by enrolled clinicians. Demographic information will be collected at baseline. Feasibility and acceptability information will be collected following the training and each of three hospice clinician follow-up visits. For outcome measures, clinician knowledge and confidence in end-of-life dementia caregiving will be collected at baseline and following training completion. FCP burden, self-efficacy, and confidence will be collected at baseline and following each of three hospice clinician follow-up visits. The VNS Health and RU research study staff will coordinate to identify when study-enrolled nurses visit study-enrolled family care partners. We will use daily automated reports from the VNS Health electronic hospice record that show names of study-enrolled FCP, dates of most recent 4 visits and visit duration for study-enrolled clinicians. As needed, information will be shared with Rutgers study personnel using encrypted email or through the VNS Health approved secure MS Teams application. This information will be transferred to the study database by VNS Health or Rutgers study personnel so that participants can be contacted by phone, personalized email, or automated email (according to their stated preference), to complete relevant data collection in a timely manner. Participants will be contacted as soon as possible following, but within 2 business days, of their last clinician/family member encounter. Rutgers and VNS Health staff will work to identify the optimal time of day to contact clinicians for follow-up. Research staff will follow up with participants by phone or videoconference as necessary to complete missing data.

**Intervention.** Clinicians in the intervention group will have access to the training and assessment tool. The training may be delivered as part of a team in-service or other meeting or clinicians may access it on their own time. If the latter, they will be asked to complete the modules within 2 weeks of access being granted. They will be asked to use the assessment tool with Black and white FCP of home hospice PLwD who will be enrolled in the study by research study team members. The tool will be used during regularly scheduled visits to the patient and at up to 3 subsequent visits. Clinicians will be provided with copies of the assessment tool to complete with FCP during visits. FCP will continue to receive standard home hospice care in addition to the intervention.

**Standard Care Control.** FCP in the standard care control group will receive home hospice services as usual. These FCP will complete the same measures as participants in the intervention condition on the same timeline using identical assessment procedures.

**Hypotheses.** >70% of clinicians will 1) complete the training, 2) use the tool as intended, 3) report the training and tool are useful, and 4) report satisfaction with the training and tool. Compared to usual care: *Feasibility/acceptability:* Clinicians who complete the training and use the tool (intervention group) will have greater knowledge of dementia-related challenges in EOL care and how to manage them. Those in the intervention group will report it helps them identify individual PLwD and FCP challenges and suggest appropriate management strategies. *Primary outcome:* FCP in the intervention group will report reduced FCP burden. *Exploratory outcomes:* FCP of intervention group will experience greater self-efficacy and preparedness. PLwD of intervention group clinicians will experience increased utilization of hospice interdisciplinary team (IDT) member services and lower rates of hospice disenrollment. Exploratory analyses will examine racial disparities in FCP burden and PLwD disenrollment.

**Measurements.** All measures will be collected by study research team members via phone call or electronic survey. All participants will be assessed on the measures listed in Table 1 (see **Appendix** for more details). FCP in both arms will be compensated $25 for an initial visit followed by $25 (e.g., by ClinCard) each time they complete a follow-up survey phone call/electronic survey, up to $100. Clinicians in the intervention arm will be compensated $25 for completing the training and $25 for each FCP with whom they use the assessment tool. Our aim is to match each clinician with up to 4 caregivers, although we anticipate some will be matched with more than 4 and as such cannot state a maximum compensation amount. Clinicians in the control arm will be compensated up to $50 for completing baseline and follow up surveys assessing knowledge and confidence in addressing dementia-specific issues in end-of-life care and for completing a brief survey following routine visits with study-enrolled FCP.

[figure not shown]

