**Aim 3.** We request the waiver to extract outcome-related information from electronic health records of home hospice patients whose FCP are enrolled in the pilot RCT (Aim 3). We will extract his information 3 and 6 months following FCP participation in the pilot RCT and so anticipate that a majority of the hospice patients for whom the information is extracted will be deceased. For these individuals, we will extract information regarding their hospice enrollment and services, including: gender, race, ethnicity, age, dates of enrollment and discharge, discharge status, care partner burden and dates recorded, care partner relationship to patient, dates and duration of hospice interdisciplinary team visits, and the clinician who made the visit.

A Request for Waiver of Authorization Form is included in the application.

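### FCP outcomes are timed by enrolled-clinician visits and the clinician post-assessment by training completion, so timing and missingness can differ by arm

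*Protocol*

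**What the plan says.** **Family care partners.** Section 3 (Aim 3: EDITH-HC pilot RCT) ties every post-baseline FCP outcome, including the primary 12-item ZBI, to a visit: "FCP burden, self-efficacy, and confidence will be collected at baseline and following each of three hospice clinician follow-up visits". The Appendix heading for the FCP assessment tools gives the same schedule, and Section 7 explains that visit dates are needed to know when to follow up. The only stated window also runs from the visit: "Participants will be contacted as soon as possible following, but within 2 business days, of their last clinician/family member encounter". Follow-up length is open: "The intervention will last for a few to several months, depending on the timing of FCP enrollment and routine hospice visits by enrolled clinicians". Controls "will complete the same measures as participants in the intervention condition on the same timeline".

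**Clinicians.** The same section says that "clinician knowledge and confidence in end-of-life dementia caregiving will be collected at baseline and following training completion". Training is given to the intervention arm only. For controls, Section 5 (Aim 3) describes the second assessment as following a presentation that the visible text does not otherwise describe or date. The knowledge hypothesis in Section 3 is worded for clinicians who complete the training and use the tool.

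**Hypotheses that bear on the trigger.** As exploratory outcomes, Section 3 expects that "PLwD of intervention group clinicians will experience increased utilization of hospice interdisciplinary team (IDT) member services", and also lower hospice disenrollment in the intervention arm.

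**The concern.** An outcome schedule should not depend on something the intervention may alter. Here the clock for the primary outcome is the visit count of an enrolled clinician. If those visits come closer together in one arm, the third follow-up falls earlier there. Section 7 expects most patients to be deceased by the time records are extracted, so elapsed time and nearness to death plausibly matter for burden. If burden rises over that period, measuring the intervention arm earlier would look like a benefit; if it falls, the error reverses. If one arm keeps more patients in hospice, more of its FCP are measured, and those never visited contribute only a baseline.

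For clinicians, an assessment triggered by completion sets those who finished training against all controls, which is no longer the randomised comparison. The pilot is meant to establish preliminary efficacy and to choose the outcome for a full trial (Section 9), so both comparisons will be used.

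**Working it through.** **1. The plan's own figure.** Section 9 gives n = [4(1−ρ)σ²(Zα/2+Zβ)²/δ²] × Vif/R. Inputs: σ = 9.8 (labelled a variance, but the figures reproduce only if it is the SD), two-sided α = 0.05, power 0.80, Vif = 1.09, R = 0.9. (1.960 + 0.842)² = 7.849.
- ρ = 0.5, δ = 6.21: 4 × 0.5 × 96.04 × 7.849 / 38.56 = 39.1; × 1.09/0.9 = 47.3.
- ρ = 0.6, δ = 5.56: 47.3.
- ρ = 0.7, δ = 4.81: 47.4.

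These agree with the stated 48 per arm. The power figures are not in dispute; they are the yardstick below. The calculation compares endpoint means and gives no attrition rate.

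**2. Timing (illustration; the protocol gives neither visit intervals nor drift).** Artefact = drift × 3 × (control interval − intervention interval).
- 14 versus 10 days: third follow-up at day 42 versus day 30, a gap of 12 days. At 0.05 to 0.15 points per day: 0.6 to 1.8 points, or 10% to 29% of 6.21.
- 14 versus 7 days: gap of 3.0 weeks. At 0.25 to 1.0 points per week: 0.75 to 3.0 points.
- 10 versus 7 days: gap of 1.3 weeks. At 0.25 to 1.0 points per week: 0.3 to 1.3 points.
- Equal intervals: zero.

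**3. Who is measured (illustration, assumed inputs).** Suppose 90% of intervention and 70% of control FCP reach the endpoint, and the unmeasured differ by 5 points. The contrast among those measured shifts by (0.90 − 0.70) × 5 = 1.0 point. The effective number per arm is 2/(1/43.2 + 1/33.6) = 37.8. At n = 48 the formula gives detectable differences of 6.17, 5.52 and 4.78; at 37.8 they become 6.95, 6.22 and 5.38.

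**4. Clinicians (from the protocol's own numbers).** The smallest counts above 70% are 9 of 12 (75%) and 13 of 18 (72%), since 8 of 12 and 12 of 18 are both 67%. Non-completers: 12 − 9 = 3 and 18 − 13 = 5.

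**The case against.** Several points on the other side are sound.

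- **Visit frequency.** A reader might infer that the protocol predicts more enrolled-clinician visits in the intervention arm. It does not. The hypothesis concerns interdisciplinary team services in general, which could rise through referral to a social worker or spiritual care counselor without changing the survey trigger. The tool is used at regularly scheduled visits and no extra visits are required. A difference by arm is a possibility, not a prediction.
- **Same timeline.** A reader might call the control-arm sentence a contradiction. It is not: both arms follow one visit-based rule. That rule aligns visit number, though, not elapsed days or the chance of being assessed.
- **Non-completers.** It is tempting to say they have no post-training data. The Appendix asks the confidence items after each relevant video, so a partial completer would have some confidence scores, and the video review form allows for videos partly watched or not watched. Staff also chase missing data. The gap is most plausible for the knowledge scale.
- **Record extraction.** Pulling records "3 and 6 months following FCP participation in the pilot RCT" may look like another visit-driven window. The extracted items are dated, so any window from FCP baseline can be rebuilt for events up to the pull. This adds no bias.
- **Unseen material.** Table 1 is not shown and may date the control clinicians' second assessment. A time axis in actual days could be set in an SAP.
- **Fixed calendar windows.** Replacing post-visit surveys entirely would put some assessments after a death, where present-tense burden items no longer fit.

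What remains is that the assessment trigger is protocol content. A mixed model may handle outcomes missing at random and can use actual dates, but it cannot recover FCP who were never contacted because no visit took place.

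**Conclusion.** The point holds as a risk built into the measurement schedule, not as a demonstrated bias. Followed as written, the plan can compare arms at different elapsed times, leave FCP without an enrolled-clinician visit unmeasured, and leave non-completing intervention clinicians without a post-training knowledge score. The last has a size from the protocol's own target: up to 3 of 12 or 5 of 18 when the target is just met, provided that not completing means no post-training knowledge survey. The primary-outcome effect has no size in the document. The 0.6 to 1.8 points, and the wider 0.3 to 3.0, rest wholly on assumed visit intervals and drift, and are zero if visits are spaced alike in both arms. The change is worth making because it is cheap; the stated sample size and detectable differences are unaffected.

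**What to change.** 1. Keep the post-visit surveys, which serve both fidelity and outcomes.
2. In the mixed model, use actual days since FCP baseline as the time axis and state the arm contrast at one common day. Report visit counts and assessment days by arm.
3. In both arms, set a fallback date and call any FCP who has had no enrolled-clinician visit by then, while the patient is alive and in hospice.
4. Collect clinician knowledge and confidence in both arms at the same fixed interval after randomisation or access, whether or not training was finished. Where clinicians train on their own time they have 2 weeks from access, so the interval should be longer than that. Give controls a matching date in place of the presentation reference.
5. Word the knowledge comparison for all randomised clinicians by arm; a completer analysis can be supportive.

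The cost is a change to the survey triggers, some protocol and SAP wording, and a few extra calls. Some of those assessments will not fall directly after a use of the tool.

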Intervention and control group FCP will be compensated up to $100 for participation in the pilot RCT: $25 for each round of data collection including baseline and up to 3 follow-up visits. Intervention group clinicians will be compensated $25 for completing the training and $25 for each FCP that they work with during the study and for whom they respond to survey questions. Our goal is to match each clinician with up to 4 caregivers, but we anticipate some will be matched with more than 4 and as such, cannot state a maximum compensation amount. Control group clinicians will be compensated up to $50: $25 for completing the baseline and post-presentation assessments and $25 for completing the post-visit assessments.

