# Aim 3. Clinician assessment tools (Pre/Post, intervention and control)

***Dementia knowledge assessment scale***

Annear, M. J., Toye, C. M., Eccleston, C. E., McInerney, F. J., Elliott, K. E. J., Tranter, B. K., ... & Robinson, A. L. (2015). Dementia knowledge assessment scale: development and preliminary psychometric properties. *Journal of the American Geriatrics Society*, *63*(11), 2375-2381.

| **Q #** | **Statements about dementia** | **Response scale**  (Please tick one box ) | | | |  |
| --- | --- | --- | --- | --- | --- | --- |
|  |  | **False** | **Probably false** | **Probably true** | **True** | **I don’t know** |
| A1 | Dementia is a normal part of the ageing process. |  |  |  |  |  |
| A2 | Alzheimer’s disease is the most common form of dementia. |  |  |  |  |  |
| A3 | People can recover from the most common forms of dementia. |  |  |  |  |  |
| A4 | Dementia does **not** result from physical changes in the brain. |  |  |  |  |  |
| A5 | Planning for end of life care is generally **not** necessary  following a diagnosis of dementia. |  |  |  |  |  |
| A6 | Blood vessel disease (vascular dementia) is the most common form of dementia. |  |  |  |  |  |
| A7 | Most forms of dementia do **not** generally shorten a person’s life. |  |  |  |  |  |
| A8 | Having high blood pressure increases a person’s risk of developing dementia. |  |  |  |  |  |
| A9 | Maintaining a healthy lifestyle does **not** reduce the risk of  developing the most common forms of dementia. |  |  |  |  |  |
| A10 | Symptoms of depression can be mistaken for symptoms of dementia. |  |  |  |  |  |
| A11 | Exercise is generally beneficial for people experiencing  dementia. |  |  |  |  |  |
| A12 | Early diagnosis of dementia does **not** generally improve quality of life for people experiencing the condition. |  |  |  |  |  |
| A13 | The sudden onset of cognitive problems is characteristic of  common forms of dementia. |  |  |  |  |  |
| A14 | It is impossible to communicate with a person who has advanced dementia. |  |  |  |  |  |
| A15 | A person experiencing advanced dementia will **not** generally  respond to changes in their physical environment. |  |  |  |  |  |
| A16 | It is important to correct a person with dementia when they are confused. |  |  |  |  |  |
| A17 | People experiencing advanced dementia often communicate through body language. |  |  |  |  |  |

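### The Aim 3 clinician-knowledge hypothesis is worded for intervention clinicians who finish the training and use the tool; tested as worded, it would compare a post-randomisation subset of one arm with usual care

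*Protocol*

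**What the plan says.** All places are in the Protocol.

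- **Randomisation and size** (Section 3, Aim 3): "The intervention will be randomized by hospice clinical team using an adaptive randomization approach". On numbers: "Approximately 12 clinicians and 48 FCP will receive the intervention and 12 clinicians and 48 FCP will receive standard home hospice care", with up to 18 clinicians per arm allowed.
- **What the intervention arm is** (Aim 3, Intervention): its clinicians are given access to the training and the tool, and are asked to finish the modules and use the tool at visits.
- **Expected uptake** (Aim 3, Hypotheses): ">70% of clinicians will 1) complete the training, 2) use the tool as intended".
- **Knowledge hypothesis** (same paragraph, in the comparison with usual care): "Clinicians who complete the training and use the tool (intervention group) will have greater knowledge of dementia-related challenges in EOL care". The next sentence, and the family care partner (FCP) and patient hypotheses, refer to the intervention group with no completion condition.
- **Timing** (Aim 3): "clinician knowledge and confidence in end-of-life dementia caregiving will be collected at baseline and following training completion".
- **Control clinicians** (Section 5, Aim 3): paid, in dollars, "25 for completing the baseline and post-presentation assessments and $25 for completing the post-visit assessments". The appendix heading over the Dementia Knowledge Assessment Scale (DKAS) covers both arms: "Aim 3. Clinician assessment tools (Pre/Post, intervention and control".
- **Status**: Section 3 lists "improving clinician knowledge and confidence" as secondary outcomes, while the Hypotheses paragraph files knowledge under feasibility and acceptability. Section 9 collects it so that the right outcome for the future full trial can be identified.
- **Analysis** (Section 9): outcomes are compared with baseline. No analysis population is stated for clinician knowledge.

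**The concern.** Finishing the modules and using the worksheet are behaviours seen only after a team has been randomised, and only in the intervention arm. A comparison restricted to clinicians who did both, against usual-care clinicians with no such restriction, no longer compares groups formed by randomisation. Clinicians who finish optional modules and take up a new worksheet may be more engaged, and engaged clinicians may know more about dementia whatever the training does. Tool use may also depend on whether a matched caregiver was available, since the protocol expects some clinicians to match with fewer than 4.

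At stake is the estimate for a secondary outcome that could help choose the endpoint of the next trial.

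**Working it through.** The protocol gives no power or precision figure for clinician knowledge. Its only power calculation concerns caregiver burden, and nothing below uses it.

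**1. Who would be left out.** Inputs: 12 or 18 clinicians per arm; targets above 70% for completion and, separately, for tool use.

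- Smallest count above 70%: 12 × 0.70 = 8.4, so 9; 18 × 0.70 = 12.6, so 13.
- If the same clinicians meet both targets: 12 − 9 = 3 left out, or 18 − 13 = 5.
- If the two groups overlap as little as possible: 9 + 9 − 12 = 6 kept of 12, or 13 + 13 − 18 = 8 kept of 18. That leaves out 6 or 10.
- If each rate is 70% and the two are independent (assumption): 0.70 × 0.70 = 49% kept. This requires 0.70 − 0.49 = 21% of clinicians to use the tool without finishing the training.

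The wording removes no control clinician in any of these cases.

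**2. Order of events.** Knowledge is re-measured once training is finished. The tool is used at patient visits after that. Membership of the hypothesis group can therefore be settled after the outcome it is used to select on. For an intervention clinician who never finishes, the text gives no follow-up time for knowledge.

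**3. Shift in follow-up scores if training has no effect.** Assume that those kept are the top fraction p on a latent engagement scale that correlates r with knowledge. The mean of those kept then moves by

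shift (SD) = r × φ(z) / p, where z is the cut-off that keeps fraction p.

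- p = 0.70: multiplier 0.497
- p = 0.49: multiplier 0.814

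False-positive rates come from a simulation with no training effect: 8,000 runs per case, those kept against all controls, two-sided t-test at 5%, clustering by team ignored.

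| Kept | Quantity | r = 0 | r = 0.2 | r = 0.3 | r = 0.5 |
|---|---|---|---|---|---|
| 70% | shift, SD | 0 | 0.10 | 0.15 | 0.25 |
| 70% | false positives, 12 per arm | 5.0% | 5.1% | 6.0% | 8.2% |
| 70% | false positives, 18 per arm | 5.1% | 5.6% | 7.0% | 9.8% |
| 49% | shift, SD | 0 | 0.16 | 0.24 | 0.41 |
| 49% | false positives, 12 per arm | 5.3% | 5.6% | 6.8% | 11.4% |
| 49% | false positives, 18 per arm | 5.4% | 6.5% | 8.4% | 15.7% |

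With 90% kept, the shift for r = 0.2 to 0.5 is only 0.04 to 0.10 SD.

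**4. Change from baseline.** If engagement correlates equally with knowledge at both times and the SDs are equal, the shift in the change score is 0.497r − 0.497r = 0. Bias then remains only if engagement also predicts change without training.

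**The case against.** The strongest reply is that the sentence is a hypothesis and not a rule for the analysis set. The bracketed label can be read as describing what that arm does, and the next sentence returns to the intervention group without conditions. Section 3 says all participants are assessed on the Table 1 measures and that staff will follow up missing data. Table 1 could not be read in the text available and may give times. Filtering on tool use that comes later is an unlikely intention. The analysis population is usually settled in the SAP, which is not at hand.

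Much of this stands. A reader might infer that non-completers will be dropped and the randomised comparison lost; no passage says so. A reader might also infer that a gain would appear even if the training did nothing. That needs engagement to be correlated with knowledge, and Section 9 plans comparison with baseline, where the bias shrinks or vanishes if engagement predicts level only. Training may be given at a team in-service, and tool use depends partly on caseload; both weaken selection by engagement.

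What does not fall away is the wording itself. The protocol defines the arm by access, sets uptake targets below 100%, and then states the between-arm prediction for those who did both things. An SAP that analysed clinicians as randomised would test a different hypothesis from the one written.

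**Conclusion.** The point holds as a wording defect that can bias one comparison. Tested as written, the knowledge hypothesis would leave out roughly 3 to 6 of 12, or 5 to 10 of 18, intervention clinicians when each target is just met, and no controls.

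The size of the bias cannot be known from the protocol, which gives no knowledge SD and no completion data. The range of 0.10 to 0.25 SD assumes 70% kept, selection strictly by engagement, correlations of 0.2 to 0.5, and comparison of follow-up scores. The 0.41 SD figure also needs 49% kept and the highest of those correlations.

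The reach is limited to clinician knowledge. A reader might extend the concern to caregiver burden, but the primary hypothesis carries no completion condition and is not touched. The change is worth making before analysis because it is cheap and because knowledge may inform the choice of the next trial's endpoint.

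**What to change.** 1. Restate the hypothesis in Section 3, Aim 3: all enrolled clinicians in teams randomised to the intervention, against all enrolled clinicians in teams randomised to usual care, whatever training or tool use they completed, adjusted for baseline DKAS.
2. Set a follow-up DKAS time in both arms that does not depend on finishing the training, for example a fixed interval from enrolment, and seek the measure from intervention clinicians who stop.
3. Report any result for completers and tool users as descriptive only, using the adherence measures already listed in Table 2 of the appendix.

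Cost: a sentence on the hypothesis, one on timing, and some effort to reach clinicians who stop. DKAS is already planned before and after in both arms, so no new instrument is needed. The estimated knowledge effect may be somewhat smaller, because it will include clinicians who did not take up the intervention.
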